##### Determination of Compliance with Dietary Supplements During Pregnancy, Infancy and Early Childhood as Well as the Consequences of Administration Difficulties to Vegan-Fed Children (Up to the Age of 5 Years)

It will be investigated whether vegans consider regular intake or administration of DS during pregnancy, infancy and early childhood to be effective. In addition, it should be clarified whether certain dosage forms (e.g., drops, pills, capsules) of existing DS for infants and children represent an unsettling factor for vegan parents, which in turn increases the risk of incorrect dosage and resulting nutrient deficiencies (e.g., wrong administration, wrong dosage). Medical experts should also evaluate the options of dosage forms and compliance as well as the consistency of administration by parents to their vegan-fed child. This should clarify whether dosage forms of DS can have an impact on the regularity of administration and subsequently on the development of nutrient deficiencies. Statements about the regularity, duration of intake and compliance of DS are intended to allow conclusions about the supply of consumers with the corresponding DS and to show any potential dangers or health-enhancing effects.

If vegans indicate a high level of compliance when taking DS, the willingness to take DS is obvious and the relevance of competent expert advice on DS can be strengthened.

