Current medical advisory conditions and sources of information for vegans are being examined in detail. The obtained results can indicate the importance of comprehensive advice from medical experts and the prevention of health risks for pregnant vegans and parents of vegan-fed children. Therefore, the study aims to highlight that a balanced, purely plant-based diet for pregnant women and children depends mainly on advice from physicians, pharmacists and dieticians. A comprehensive specialist knowledge about a vegan diet and DS among medical experts is the basic prerequisite for competent information provision and as a result essential for a low-risk vegan pregnancy and childhood. The study results are intended to encourage medical experts to provide comprehensive advice to vegans to be able to support pregnant women and parents of vegan-fed children as best as possible during these vulnerable life stages. As the number of vegans is constantly increasing, expertise about a vegan diet and DS should be expanded among physicians, pharmacists and dieticians and made permanently available.

For this reason, the following objectives were defined:

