### 2.7. Statistical Methods and Data Analysis

The survey data will first be exported from LimeSurvey to Excel (Microsoft Corp., Redmond, WA, USA) and then analyzed using IBM SPSS Statistics version 31 (IBM Corp., Armonk, NY, USA) and R version 4.5.1 (R Core Team). Descriptive statistics will be used to summarize the results. For example, averages and standard deviations will be calculated for numeric variables, while frequencies and percentages will be reported for categorical data. Diagrams such as bar charts and boxplots will visualize the results. Depending on the type of data, different methods will be used to compare groups. Categorical variables will be analyzed using chi-square tests, and continuous variables with ANOVA. For yes/no outcomes (such as whether participants use DS or whether medical experts recommend them) logistic regression models will be applied to examine possible influencing factors. We plan to use both simple (univariate) and more complex (multivariate) logistic regression models. In the multivariate models, we will include relevant background characteristics like age, gender, education, household situation, or medical profession to better account for possible confounding effects. Since the study is exploratory, *p*-values will be reported descriptively. There will be no correction for multiple testing. Comparisons between groups will be carried out only when there is a sound theoretical reason and enough data to support it.

Possible comparisons within the vegan participant group include

-People living in rural vs. urban areas;-Supplement users vs. non-users (for themselves or their children);-Participants who changed their diet during pregnancy vs. those who did not;-Individuals who received professional advice vs. those who used informal sources like social media.

Possible comparisons within the group of medical experts include

-Those who support vs. those who reject vegan diets during pregnancy and childhood;-Those who advise supplementation vs. those who discourage it;-Differences between professions (e.g., pediatricians, pharmacists, dietitians).

Depending on the final data, additional group comparisons will be added. We will only report comparisons that are well justified and provide useful insights.

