### 3.2. Secondary Outcome Measures

Secondary outcome measures include gathering information on socio-economic factors such as age, gender, highest educational attainment, place of origin (urban/rural), household size, and pregnancy status. This data is collected to link these variables with responses on vegan diets and dietary supplement usage, to identify and cluster behavioral patterns among vegans. Additionally, medical experts such as physicians, pharmacists, and dietitians are asked about their practice location (postal code) and, in the case of physicians, their specialty (gynecology, pediatrics, or general medicine) to understand how these factors might influence their perspectives, similar to the approach taken with vegan participants.

Secondary outcome measures for vegans are as follows: assessment of health perceptions during pregnancy and childhood, evaluation of perceived health benefits associated with a purely plant-based diet, and the interpretation of their own vegan lifestyle: This includes factors such as frequency of dietary exceptions, perceived health benefits of veganism, duration of adherence to a vegan diet, whether vegans maintained a vegan diet during one or more pregnancies, and any potential influences or reasons that may have hindered or altered their dietary choices. Other aspects include understanding of DS (such as perceived effectiveness, categorization, selection criteria), self-reported compliance, consistency of supplement administration by parents to vegan-fed children, support or opposition to supplement use during pregnancy and childhood, data on dosage estimations, challenges with administration based on form (e.g., syrup, capsules, tablets), evaluation of nutritional needs for vegan pregnancy and childhood, willingness to receive guidance on vegan nutrition during pregnancy and early childhood, and subjective trust in advisory sources regarding a vegan diet during these stages.

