
Research gaps concerning the administration of DS, the consistency of taking them and compliance shall be closed by statistically evaluating data from performed surveys (vegans, pediatricians, gynecologists, general practitioners, pharmacists, and dieticians). In addition, causes for the intake or rejection of DS (from a social and socio-demographic perspective) are to be examined. Resulting risks concerning the supply of nutrients are to be determined as well as the role that information sources play in this context. It is precisely these unanswered questions that underline the relevance of the VedieS study, as they are directly related to risk prevention. According to a recent study by Meulenbroeks et al. [61], pregnant women following a vegan diet often receive limited or no specific dietary guidance from obstetric healthcare providers. Only 19% of participants reported having received nutritional counseling that was specific to their needs during pregnancy. The VedieS study’s approach to identifying the cause of nutrient deficiencies during vegan pregnancy and childhood, due to a fundamental lack of information, is new and can be important for preventing health risks for vegans. Unsupplemented vegan pregnancies are associated with a higher risk of adverse outcomes [45]. These findings highlight the importance of guideline-based supplementation for vegans during sensitive life stages. The quality of the information sources used by vegans is most likely dependent on the existing attitude of the information providers. If medical experts have a negative attitude towards a vegan diet and DS, their advice may be inadequate—either due to a lack of knowledge about a purely plant-based diet, or because a vegan diet is discouraged per se without providing additional information. Knowledge gaps regarding vegan diets remain common among medical experts, likely due to limited nutrition education and a lack of familiarity with plant-based dietary patterns [44,60]. As a result of limited professional support, many vegan pregnant women turn to alternative sources of information such as books, online platforms, or peer communities to address their specific dietary needs [61]. It is important to know exactly where the information received comes from in order to be able to draw conclusions about its safety and reliability. In a cross-sectional online survey by Fuschlberger et al. [62] among Austrian vegans, 92% reported taking vitamin B_12_ through DS or fortified foods, yet fewer than 10% had consulted a medical expert. However, more research is needed to find out exactly which specific sources of information are being used.

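### High compliance among supplement takers does not show willingness among all vegans and, without a comparison by advice received, says nothing on the relevance of expert advice

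*Protocol article*

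**What the plan says.** The protocol article's secondary objective on DS compliance (Section 2.1.2) ends with an interpretation: "If vegans indicate a high level of compliance when taking DS, the willingness to take DS is obvious". The sentence goes on to say that "the relevance of competent expert advice on DS can be strengthened".

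Four other places bear on it:

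- Section 2.7 lists among the possible comparisons within the vegan group "Supplement users vs. non-users (for themselves or their children"). It also lists people who had professional advice against people who relied on informal sources.
- Section 3.2 lists "support or opposition to supplement use during pregnancy and childhood" as a secondary outcome, alongside self-reported compliance and distinct from it.
- Section 4 cites a survey: "among Austrian vegans, 92% reported taking vitamin" B12 "through DS or fortified foods, yet fewer than 10% had consulted a medical expert".
- Section 2.1 gives the wider purpose: "the study aims to highlight that a balanced, purely plant-based diet for pregnant women and children depends mainly on advice from physicians", with pharmacists and dieticians named next.

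**The concern.** The sentence contains two inferences, and neither follows from a compliance figure alone.

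**From compliance to willingness.** As worded, the measure describes people who are taking or giving DS. Those who avoid or reject DS are the people whose willingness is in doubt, and the measure does not describe them.

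**From compliance to expert advice.** A high level of compliance bears on the relevance of professional advice only if it is set against the advice that respondents received. The sentence makes no such comparison.

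If the results are written up as this sentence suggests, willingness would be overstated whenever a real share of respondents do not use DS. A practical message about expert advice would also be drawn from a number that does not carry it.

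**Working it through.** The protocol attaches no figure to this sentence, so there is nothing to reproduce. Two short calculations and one comparison of sections show the point.

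**1. Conditioning on use.**

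Formula: share of all respondents with regular intake = (share who take or give DS) × (share compliant among takers).

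Inputs: 90% compliance among takers, and uptake of 50%, 70%, 92% or 100%. All of these are assumptions. The document gives neither quantity for this population. The counts use the target of 1000 vegan participants in Section 2.6.1, for scale only.

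| Assumed uptake | Calculation | Regular intake among all | Non-users per 1000 |
|---|---|---|---|
| 50% | 0.50 × 0.90 | 45% | 500 |
| 70% | 0.70 × 0.90 | 63% | 300 |
| 92% | 0.92 × 0.90 | 83% (0.828) | 80 |
| 100% | 1.00 × 0.90 | 90% | 0 |

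The same compliance among takers fits regular intake anywhere from 45% to 90% of the sample. Only when everyone uses DS do the two figures agree.

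**2. Are willingness and compliance one measure in this protocol?** No. Section 2.7 expects enough non-users to form a comparison group. Section 3.2 collects attitude to DS as an item of its own. The article therefore has a direct measure of willingness and does not need to infer it from compliance.

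**3. Intake and expert contact in the cited survey.**

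Inputs from Section 4: 92% with B12 intake, and fewer than 10% who consulted a medical expert. Assumption: both percentages share one denominator.

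- Intake without consultation: at least 0.92 − 0.10 = 0.82, so at least 82% of respondents.
- Consulted, among those with intake: at most 0.10 / 0.92 = 0.109, so at most 10.9%.

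In that survey, high intake occurred largely without expert consultation. The figures have limits. They concern B12 only, pool DS with fortified foods, describe Austrian vegans in general rather than pregnant women or parents, and measure intake rather than compliance. They illustrate that intake can be high with little expert contact, and nothing beyond that.

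**The case against.** The strongest reply is that this is a closing remark under a secondary objective of an exploratory, descriptive study. It sets no denominator, threshold or decision rule, and the analysis section (2.7) does not repeat it. That is correct, and it limits the weight of the point. The remark still says in advance how a listed outcome will be understood.

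The compliance items (category J, Section 2.5) are in supplementary material that is not shown here, so non-takers might be able to answer them. This also stands. The point rests on the sentence as worded, not on a known questionnaire filter.

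Much of the remedy is already in view. Section 2.7 lists users against non-users and professional against informal advice, and Section 3.2 covers attitude. A reader might infer that people who reject DS are lost from the study; they are not. However, the comparisons are listed only as possible ones, and neither is tied to the reading of compliance.

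A reader might also take the cited survey to contradict the sentence. It does not. The sentence can mean that regular users are willing users who would benefit from good advice on selection and dosing, and high intake with few consultations is compatible with that. On this milder reading the second inference is less objectionable, but the first is unaffected.

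**Conclusion.** The point holds as a correction to how one secondary outcome is to be interpreted. Compliance among takers does not establish willingness among all vegans, and a compliance level not compared by advice received does not by itself support a statement on the relevance of expert advice. Because the study is exploratory and the sentence is not an analysis rule, the weight is modest, but the correction is worth making.

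The size cannot be derived from the document. The 45%, 63% and 83% are illustrations that depend wholly on the assumed 90% compliance and the assumed uptake.

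Two stronger readings are tempting and are not supported:

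- **That no result could count against the study's message.** The sentence gives no reading for low compliance, so this cannot be shown from it. The aim stated in Section 2.1 is a separate matter.
- **That 90%, or any takers-only figure, will be reported as willingness among all vegans.** Nothing in the document says so.

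**What to change.** Replace the closing sentence of the compliance objective in Section 2.1.2 with a reporting rule, applied separately to pregnancy and to the child:

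1. Uptake of DS, and support for or opposition to DS, among all eligible respondents.
2. Compliance among takers, with its denominator stated.
3. Regular intake among all eligible respondents, with non-takers counted as not taking.

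Base any statement on expert advice on the professional versus informal advice comparison already listed in Section 2.7, applied to uptake (item 1) and regular intake (item 3). State in advance that equal or higher values without professional advice do not support the statement.

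The cost is a rewording, a changed denominator and a little more tabulation. No new data should be needed if use, compliance and source of advice are collected, as Sections 2.7 and 3.2 indicate. The downside is that the compliance-based figure becomes less favourable.

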##### Investigate if Gender-Specific and Socio-Demographic Differences Within the Group of Vegans Exist

Different perceptions of and opinions on a vegan diet and DS (during pregnancy, infancy and early childhood) between vegan women, men, diverse people as well as between vegans in and outside the city should clarify differences in nutrient deficiency-associated risks of a vegan diet and the intake of DS. Other socio-demographic characteristics such as age, education, income, and employment status should also be included. Risk deviations could exist due to unequal access to information.

The goals of the VedieS study are to

Illustrate the importance and necessity of comprehensive advice on DS from medical experts;Reduce the risk of malnutrition of vegans by encouraging physicians, pharmacists and dieticians to provide competent advice;Promote further training on the knowledge of a vegan diet and DS among medical experts;Increase the willingness to optimize the food and nutritional health literacy of pregnant vegans and parents of vegan-fed children and raise their awareness of its importance.

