### 2.4. Eligibility Criteria

Inclusion criteria for vegans:1.Females/diverse participants (ages 18 and over) who follow/followed a vegan diet during their pregnancy/pregnancies (if there is/was more than one pregnancy, at least during one of their pregnancies).2.Parents (female/male/diverse—ages 18 and over) who feed/fed their child/children (if there is more than one child, at least one of them) a vegan diet at least between the ages of 0 and 5 years.3.Vegan mothers/diverse participants (ages 18 and over) who breastfeed/breastfed their infant(s)/child(ren). Answering questions regarding their infant(s)/child(ren) up to the age of 5 years will be included.4.Pregnant and breastfeeding women/gender diverse participants/parents (f/m/d) who make rare exceptions to their vegan diet and a vegan diet of their child(ren)—up to the age of 5 years. Inclusion in the survey depends on the frequency of exceptions → determined through questions/given answers within the survey. Participants that consume animal products a maximum of twice a month will be included; hence, participants who do not make vegetarian, pescetarian, or omnivorous exceptions more than twice a month will be included.5.Confirmation of the participant information (online—addressing the subjects, purpose and process of the study, opportunities for discussion of further questions, duration of the questionnaire, who is conducting the study, possibility for further inquiries).

Exclusion criteria for vegans:1.Females/diverse participants who change/changed their vegan diet (eat/ate a vegetarian or omnivorous diet) during their pregnancy/pregnancies.2.Parents who do not feed/have never fed their children a vegan diet at least up to the age of 5 years (if vegan mothers followed a vegan diet during their pregnancy, exclusion only relates to questions concerning their children).3.No confirmation of the participant information (online).

For inclusion in the study, at least one inclusion criterion (plus participant information) must be fulfilled. Exclusion (or not inclusion) will happen if only exclusion 3 is fulfilled. If only 1 or 2 is fulfilled, and 3 is not, participants will be included in the survey.

Inclusion criteria for medical experts:1.Gynecologists, pediatricians, general practitioners, pharmacists, and dieticians with or without a consulting focus on vegans.2.Confirmation of the participant information (online).

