### 5.2. Limitations and Strengths of the Study

Since the study is based on survey responses, there is a possibility of over- or under-reporting due to the subjective self-assessment of participants regarding, e.g., compliance when taking DS, parental administration consistency and correct dosage of DS, the frequency of exceptions to a vegan diet, and the period within parents and children already follow a vegan diet. Data is based on participants’ motivation to self-report. Hence, only responses from actual participants are considered which does not necessarily capture the opinion of all vegans and medical experts. Although all genders are included, it is likely that women will be overrepresented, because of the focus on pregnant/breastfeeding women and secondarily vegan parents. Nonetheless, the strengths of this study outweigh its limitations. This is the first time data has been collected considering perspectives of both vegans and different medical specialists regarding a vegan diet and DS during pregnancy and childhood. Resulting insights could help to shift experts’ attitudes from rejection of a fully plant-based lifestyle and the refusal of information provision on a vegan diet and DS during these life stages to more comprehensive, informed guidance for vegans. Experts’ acceptance of the need and the willingness for detailed advice can be promoted which could cause distancing from devaluing a vegan lifestyle. The value of gathering these fresh data on public health nutrition ultimately outweighs limitations as results provide significant benefits to both vegans and medical experts alike.

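### A whole-sample gender comparison mixes gender with entry route, because men can enter only as parents while women and diverse participants can also enter by vegan pregnancy or breastfeeding alone (minor)

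*Protocol article*

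**What the plan says.** Section 2.1.2 of the protocol article sets a secondary objective on gender-specific and socio-demographic differences. It compares perceptions and opinions "between vegan women, men, diverse people as well as between vegans in and outside the city", covering pregnancy, infancy and early childhood, and intends the result to clarify differences in deficiency-related risk and supplement intake.

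Section 2.4 defines who can be in those groups:

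- Criterion 1 (pregnancy): "Females/diverse participants (ages 18 and over) who follow/followed a vegan diet during their pregnancy/pregnancies".
- Criterion 2 (parents): "Parents (female/male/diverse—ages 18 and over) who feed/fed their child/children" a vegan diet.
- Criterion 3 (breastfeeding): "Vegan mothers/diverse participants (ages 18 and over) who breastfeed/breastfed their infant(s)/child(ren").
- Criterion 4 (rare exceptions): "Pregnant and breastfeeding women/gender diverse participants/parents (f/m/d) who make rare exceptions to their vegan diet and a vegan diet of their child(ren").

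The criteria are alternatives: "at least one inclusion criterion (plus participant information) must be fulfilled". Exclusion criterion 2 concerns parents without a vegan-fed child. For mothers who were vegan in pregnancy it removes only the questions about children, and the rest of their answers stay in.

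Section 2.7 gives examples of covariates for the multivariable models ("age, gender, education, household situation, or medical profession"). Entry route and parent status are not among them, and gender is not in its list of possible group comparisons. Section 5.2 says that "it is likely that women will be overrepresented" and attributes this to the focus on pregnancy and breastfeeding. Section 3.2 lists pregnancy status among the variables collected.

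**The concern.** The men in the sample are all parents of vegan-fed children. The women are a mixture: some are such parents, and some qualify only because they were vegan in a pregnancy or while breastfeeding. If these two kinds of respondent answer differently, women and men will differ overall even when mothers and fathers in the same position answer alike.

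At stake is the reading of that difference. Section 2.1.2 already suggests that unequal access to information may explain differences in risk, so a gap produced by entry route could be taken as support for that explanation. The acknowledgement in section 5.2 concerns how many women there will be, not whether the women and men are comparable. A larger sample does not shrink this kind of bias.

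**Working it through.** There is no stated figure to reproduce, because the article gives no breakdown by gender or entry route. The check is a reading of the criteria, followed by an illustration on assumed inputs.

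**Routes open to each gender (section 2.4)**

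| Route | Women | Diverse | Men |
|---|---|---|---|
| 1 Vegan pregnancy | yes | yes | no |
| 2 Parent of vegan-fed child | yes | yes | yes |
| 3 Breastfeeding | yes | yes | no |
| 4 Rare exceptions | yes | yes | only as parents |

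One criterion is enough, so a woman can be in the sample by route 1 or 3 alone. No man can. Routes 1 and 3 have no male counterpart, so adjusting for route cannot create a comparison there. The parent route is the only one on which all genders can be compared.

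**Which items are exposed**

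- Child-feeding items: women who were vegan in pregnancy but have no vegan-fed child are dropped from these by exclusion criterion 2. Some exposure may remain through criterion 3, which keeps answers about the children of breastfeeding participants.
- Items put to all vegan respondents: views on the diet and on supplements, information sources, trust, own supplement intake. Nothing in section 2.4 or 2.7 separates the routes for these.

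**Size of the artefact**

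Let w be the share of women who enter only by pregnancy or breastfeeding, p the proportion giving an answer among parents of either gender (no true gender effect), and p + d the proportion among the pregnancy- or breastfeeding-only women.

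- Men: p
- Women: (1 − w) × p + w × (p + d) = p + w × d
- Apparent gender difference: w × d

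With the assumed values p = 80% and p + d = 95%, so d = 15 points:

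- w = 30%: 0.30 × 15 = 4.5 points
- w = 50%: 0.50 × 15 = 7.5 points
- w = 70%: 0.70 × 15 = 10.5 points

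Over a wider assumed range, w = 20% with d = 10 points gives 2 points, and w = 60% with d = 30 points gives 18 points. If d is zero the artefact is zero, and if d is negative it reverses. None of these inputs is in the documents.

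**After the restriction**

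Among parents only, w = 0, so w × d = 0.

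**Cost in precision**

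With equal outcome variance in both groups, the standard error of a difference is proportional to √(1/men + 1/women). Take an assumed 100 men among the target of 1000, and the same three shares of women removed:

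- All 900 women: √(1/100 + 1/900) = 0.1054
- 630 women left (30% removed): 0.1076, which is 2% larger
- 450 left (50% removed): 0.1106, which is 5% larger
- 270 left (70% removed): 0.1171, which is 11% larger

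**The case against.** The strongest reply is that the article commits to no faulty analysis. It states an objective, does not list gender among the possible comparisons in section 2.7, makes comparisons conditional on a sound reason and enough data, reports p-values descriptively, and gives its covariates only as examples. A separate analysis plan may restrict the comparison. The variables needed to separate the routes are being collected. All of this stands, and it is why the point is minor. It does not remove the point, because the objective and the eligibility rules are both stated here and, taken together, do not support a gender contrast over all vegan respondents.

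Three stronger readings are tempting and should not be drawn:

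- A reader might infer that child-feeding comparisons are equally affected. Exclusion criterion 2 already takes women without a vegan-fed child out of those questions.
- A reader might infer that gender as a covariate in models of pregnancy outcomes carries the same fault. Men have no pregnancy of their own and contribute no records to such a model, so their entry route cannot distort it. Section 2.7 also names no such model.
- A reader might infer that the comparison could detect only large differences anyway. That depends on the number of men and on the base rate of each answer, and the article gives neither.

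**Conclusion.** The point holds for items put to all vegan respondents: a whole-sample contrast between women, men and diverse people confounds gender with entry route. This follows from the wording of sections 2.1.2 and 2.4 alone. The size does not. It is w × d, and the 4.5 to 10.5 points shown rest entirely on assumed shares and an assumed 15-point difference between routes. Severity is minor: one secondary, exploratory objective is affected, and the problem can be removed at analysis. The documents do not support saying that the gender objective cannot be met. It can be addressed among parents.

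**What to change.** In section 2.7, state that gender comparisons are made among respondents who meet inclusion criterion 2 (with the parents whom criterion 4 admits with rare exceptions), and only on items put to all of them. In section 5.2, add that gender differences over the whole sample are not like for like, because the routes of entry differ by gender. Adjustment for the child's age is optional.

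The cost is one or two sentences in 2.7 and one in 5.2. No new data are needed: section 2.3 says that the questionnaire itself determines eligibility, and pregnancy status is collected. The downside is fewer women in this one comparison. If men are the smaller group, as section 5.2 leads one to expect, the loss of precision is small. The restriction removes the entry-route component only, and the contrast among parents remains an observational one.
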